### Setting and recruitment

All study aims will be conducted in pediatric primary care practices affiliated with two large academic medical centers in PA. The affiliated pediatrics practices in western PA serve over 70% of youth in the region and include 32 practices across 54 office sites in nine western PA counties. This group of practices serves over 266,000 privately and publicly insured patients, aged birth to 21 years. The second affiliated primary care network in eastern PA is the largest provider of primary care services in the region, with 31 practices across five counties. Clinicians in the network serve over 249,000 private and publicly insured patients, aged birth to 21 years. For each study aim, we will obtain caregiver/guardian consent, adolescent assent and/or consent for adolescents aged 18 years.

To ensure that the participant groups (adolescents, caregivers, and primary care clinicians) across study aims are reflective of the target clinical population and implementation context, we will recruit participants as part of routine well child visits. Prior to visits, potentially eligible patients based on electronic health record (EHR) screening will receive an email jointly signed by a primary care practice champion at the family's care site and research staff providing information about the research. During well child visits, the Patient Health Questionnaire (PHQ-9-M) (81) depression screener is administered as part of standard practice and integrated into the EHR. For all study phases, we will implement EHR-based clinician-directed alerts if patient scores meet criteria for potential enrollment based on their depressive symptoms. If the patient and family are interested in the research, we will conduct either in-person or remote informed consent procedures to maximize flexibility for participants. Throughout study phases, we will monitor the recruitment of Black and/or Hispanic/Latinx adolescents and caregivers and meet regularly with primary care clinical teams to solicit ongoing feedback on recruitment procedures and adjust these methods as needed to recruit a diverse sample. The protocol for this study was approved by the Institutional Review Boards of the affiliated academic medical centers. The following sections detail additional methods by aim.

### Aim 1: Initial qualitative inquiry

#### Aim 1 participants

Aim 1 participants will include 10 adolescents, 10 caregivers of adolescents, and 10 primary care clinicians, including physicians and behavioral health providers, who are working at the affiliated primary care sites. We aim to recruit a sample with at least 50% of adolescent and caregiver participants self-identifying as Black and at least 10% self-identifying as Latinx. Adolescent inclusion criteria are as follows: age 12–18 years; able to understand and converse in English; and evidence of moderate-severe depression (PHQ-9-M >11) (81) and clinically significant sleep disturbance (PHQ-9-M sleep item 3 [“trouble falling or staying asleep”] >2, sleep trouble >50% of days in past 2 weeks). Participants with a life-threatening medical condition requiring immediate treatment or intellectual or developmental disability precluding comprehension of study procedures will be excluded, as will adolescent participants with diagnoses of obstructive sleep apnea, restless legs syndrome, bipolar disorder, a current manic or psychotic episode (per participant or caregiver report or medical record review).

#### Aim 1 measures

Interview guides will be developed with input from key informant groups, including adolescents, caregivers, providers, and health systems leaders to ensure the most relevant information is gathered. The dimensional CFIR framework (61) will guide interview questions on multi-level barriers and facilitators to TSC content and delivery strategies. More specifically, in the CFIR domain of intervention characteristics, we will solicit perspectives on the relative advantage of implementing TSC in primary care vs. other outpatient settings, the extent to which the content would require adaptation to meet adolescents' needs, and the ways in which the intervention is packaged and delivered to youth. Related to the CFIR outer setting domain, we will ask interviewees about the needs and resources of adolescents seen in the primary care sites. Inner setting questions will inquire about the norms and values of the primary care setting and the climate for implementation (61). This includes questions about the likelihood of future intervention implementation, dissemination, and sustainment (82) in primary care after the research concludes. In the CFIR domain of individual characteristics we will solicit perspectives about adolescents' sleep-related knowledge, beliefs, and attitudes, as well as their views of the TSC intervention content and planned delivery methods. We will embed a health equity perspective (59) and assess youth experiences of personally-mediated and systemic/institutional racism and discrimination, the impacts of these experiences on sleep, and their perceptions about addressing the sleep impacts of these experiences through TSC (31–34).

#### Aim 1 analytic approach

The sample size for this aim was based on guidelines for thematic saturation in qualitative research (83). We will focus our analysis on the *a priori* attributes of interest, specifically CFIR domains, TSC barriers, and potential adaptations (84, 85). We will initially analyze interviews using Rapid Qualitative Analysis (86), to facilitate the rapid analysis and iterative adaptation of intervention content and delivery strategies. During data collection and analysis, we will assess for thematic saturation and for a diversity of perspectives given the small number of participants proposed and the focus of this research on racially and ethnically minoritized youth. If necessary, we will increase our sample size to maximize the inclusion of a wide range of perspectives within and across key informant groups. To incorporate qualitative data from the different interview groups (adolescents; caregivers; clinicians) we will follow NIH guidelines (87) and mixed methods approaches (88) to stratify the themes that emerge according to informant groups. This will require interview transcription, the iterative development of a codebook, and the coding of qualitative data in a specialized software program.

### Aim 2: Iterative TSC adaptation

#### Aim 2 participants

We will recruit 15 adolescents (at least 50% self-identifying as Black; 10% self-identifying as Latinx) in three cohorts of five adolescents each to participate in iteratively adapting and testing TSC. Aim 2 inclusion/exclusion criteria are identical to those in Aim 1.

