**Optional modules**		
Improving sleep efficiency	Adjust recommendations and increase problem-solving for social and environmental sleep disruptors, including light, noise, neighborhood, and family factors	• Adolescent sleep associated with social (safety, crime) and environmental (light, noise) neighborhood factors (27). • Family environment can reduce youth sleep efficiency (29).
Reducing time in bed	Problem-solve limited opportunities for time out of bed based on sleep space and family context	• Family factors can impact youths' ability to remain out of bed (e.g., room-/bed-sharing) (29).
Dealing with delayed or advanced phase	Provide evening blue blocker glasses and morning re-timer goggles+ (71).	• Neighborhood-level variation in light exposure (27). • Sleep environment factors (e.g., room-/bed-sharing) (28, 29).
Reducing sleep-related worry/vigilance	Apply cognitive strategies (coping, restructuring) to address pre-sleep worry/vigilance related to racism, discrimination, and neighborhood safety concerns	• Racism, discrimination, neighborhood violence linked with poor sleep quality and bedtime hyperarousal (36, 38, 39). • Targeting these may benefit sleep onset and quality

+ indicates adaptation made during open pilot of TSC.

Participant inclusion criteria were age 13–18 years, able to understand and converse in English, receiving care at a specialty clinic for youth at high risk for STB, with current moderate sleep disturbance [Pittsburgh Sleep Quality Index (72) global score >8], current suicidal ideation (per clinician report or self-report), depression, and a parent/guardian willing to consent for research. Adolescents were excluded if they had a bipolar disorder diagnosis, or were taking any photo-sensitizing medications (e.g., neuroleptics and antiarrhythmic drugs), as the bright light administered in in our adapted version of TSC is contraindicated with these medications. Participating parents/guardians provided informed consent and adolescents provided assent; youth who were age 18 or turned 18 during the study provided informed consent. Participants wore a wrist actigraph (CentrePoint Insight Watch, Actigraph Corp, Pensacola FL), completed daily sleep diaries (items described elsewhere), and attended TSC sessions every 1–3 weeks with a master's level study clinician, who delivered the program as an adjunct to youths' behavioral healthcare in the specialty clinic. The study was approved by the Institutional Review Board.

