#### Aim 2 measures

The primary Aim 2 outcomes pertain to intervention acceptability and feasibility. We will also pilot the sleep data collection methods and strategies to increase morning bright light and decrease evening light in anticipation of the Aim 3 randomized trial. Adolescents will wear actigraphs, Re-Timer glasses in the morning, blue-blocker glasses in the evening, complete a daily sleep diary, and provide ratings of their perceived sleep disturbances at pre and post intervention.

*Intervention acceptability* will be assessed at post-intervention using the adolescent self-reported Acceptability of Intervention Measure (AIM) (89). We will also conduct semi-structured qualitative interviews to identify participants' perspectives about intervention acceptability, barriers, and recommendations for additional adaptations to content or delivery strategies.

*Intervention feasibility* will be indexed by multiple outcomes (90), including the number of TSC sessions attended and rates of intervention attrition, to index intervention engagement. Intervention fidelity will be measured *via* the coding of a randomly selected 10% of video recorded TSC sessions. Sessions will be coded using the Cognitive Therapy Scale (CTS) (91) and a TSC session checklist (92), both used in prior TSC research.

*Actigraphy* is a widely used method of assessing sleep and circadian disruptions longitudinally in an individual's natural environment. Actigraphy is well-validated validated against polysomnography, the gold standard measure of overnight sleep (93). Consistent with guidelines, adolescents will continuously wear an actigraph on their non-dominant wrist, unless bathing or swimming, and complete a corresponding sleep diary for actigraphy scoring purposes. Sleep diary ratings will include time in and out of bed, sleep onset latency, night awakenings, and sleep quality (94). Actigraphy data will be scored using the Cole-Kripke algorithm in ActiLife software, which are validated against polysomnography and other actigraphs in young adults (95) and adolescents (96).

*Self-reported sleep disturbances* will be measured using the well-validated pediatric Patient-Reported Outcomes Measurement Information Systems (PROMIS) Sleep Disturbance and Sleep-Related Impairment Scales (97), which respectively measure perceived sleep difficulties and the impacts of sleep on daily functioning.

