#### Aim 2 intervention procedures

TSC study clinicians will review the intervention manual and attend an initial 1-day training with the study investigators, who will conduct weekly supervision. The TSC developers ([name] and [name]) will consult on implementation as needed. Clinicians will interface with adolescents' other treatment providers and/or their caregivers in line with preferences identified in Aim 1. Therapist fidelity ratings (described above) will be monitored, with ratings < 80% prompting re-training with study investigators.

Study clinicians will implement core and optional modules weekly over 6–8 weeks *via* a HIPAA-compliant, secure telehealth platform. TSC sessions will supplement other mental health treatment that participants may be receiving. The selection and individualization of TSC models will be guided by the intake assessment, case conceptualization, adolescents' ongoing reports of sleep disturbances at sessions, and their actigraphy and daily diary data.

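### Aim 2 gives adolescents a bright-light device that the article says is contraindicated with photo-sensitizing drugs, but its eligibility criteria do not exclude users of those drugs

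*Protocol article*

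**What the plan says.** In Initial pilot findings, Methods (the paragraph after Table 1), adolescents were excluded for bipolar disorder or if they "were taking any photo-sensitizing medications (e.g., neuroleptics and antiarrhythmic drugs". The reason given for the second exclusion is that "the bright light administered in in our adapted version of TSC is contraindicated with these medications".

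Aim 1 participants excludes people with an immediately life-threatening medical condition or with an intellectual or developmental disability that prevents them from understanding the procedures, "as will adolescent participants with diagnoses of obstructive sleep apnea, restless legs syndrome, bipolar disorder, a current manic or psychotic episode". No criterion concerns medication.

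Aim 2 participants reads: "Aim 2 inclusion/exclusion criteria are identical to those in Aim 1". Aim 3 participants and randomization says the same of the trial. Aim 2 measures states: "Adolescents will wear actigraphs, Re-Timer glasses in the morning, blue-blocker glasses in the evening". The same section says that the study will pilot "strategies to increase morning bright light and decrease evening light in anticipation of the Aim 3 randomized trial". On concurrent care, Aim 2 intervention procedures states: "TSC sessions will supplement other mental health treatment that participants may be receiving".

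**The concern.** The contraindication concerns a device and a class of drugs. It does not depend on the specialty clinic where the pilot ran, so it should follow the device into any later phase that uses it. Instead, the criteria for an interview study, where no light is given and the omission is harmless, are reused unchanged for a phase in which participants wear the device.

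What is at stake is the safety of minors. The pilot offers no reassurance, because it excluded these adolescents and its experience with the light component therefore does not cover them.

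**Working it through.** The plan gives no figure to reproduce; the check is a comparison of the article's own statements.

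**Criteria against device use**

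| Phase | Medication exclusion | Bipolar exclusion | Bright-light device |
|---|---|---|---|
| Open pilot | Yes | Yes | Yes, target 30 min each morning |
| Aim 1 | No | Yes | No (interviews) |
| Aim 2 | No (same list as Aim 1) | Yes | Yes, stated without condition |
| Aim 3, TSC arm | No (same list as Aim 1) | Yes | Probable, not stated |

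The bipolar exclusion was carried forward from the pilot; the medication exclusion was not.

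**Do the remaining exclusions close the gap?** Only in part. Excluding bipolar disorder and current manic or psychotic episodes removes some users of neuroleptics. An adolescent with neither diagnosis who takes a neuroleptic still passes, as does anyone on an antiarrhythmic who has no other exclusion. The pilot applied the bipolar and medication exclusions side by side, so the first was not treated there as enough. Participants may also stay in other mental health treatment, so concurrent prescribing is foreseeable.

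**Is there another safeguard?** None is described. Aim 3 participants and randomization and Aim 3 measures provide for tracking treatment and medication, but attach no screen and no rule for withholding the device. Medication measurement is not described for Aim 2.

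**How firm is the extension to Aim 3?** For it: Aim 2 pilots the light strategies with the trial in view, and Aim 3 intervention procedures carries over the Aim 2 procedures for TSC. Against it: Table 1 lists the step ("Provide evening blue blocker glasses and morning re-timer goggles") under an optional module, and the Design section leaves the final TSC content to the earlier aims.

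**Numbers covered by the gap**

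- Aim 2: 3 cohorts × 5 = 15.
- Aim 3 ceiling: 75 × 2/3 = 50, the TSC sample size given in Aim 3 analytic approach. This is an upper bound, and fewer would be exposed if the light stays optional.

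**Exposure, if the pilot's 30-minute target carries over to a 6–8 week course.** This is an assumption; the Aim 2 text states no dose. 30 min × 42 days = 1260 min = 21 h, and 30 min × 56 days = 1680 min = 28 h. At the pilot's 56% adherence (from completed diary days), this becomes 21 × 0.56 = 11.8 h to 28 × 0.56 = 15.7 h. These hours describe planned use, not risk, and the finding does not depend on them.

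**The case against.** The strongest reply is that what is missing may be a device rule rather than an eligibility criterion, and that an article can leave such a rule to the full protocol or the intervention manual. Module selection is guided by an intake assessment and case conceptualization, and the goggles sit in an optional module. Electronic record screening, medical record review and clinician contact with other providers are further points at which a prescription might be noticed.

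Part of this stands. Identical criteria would be acceptable if a withholding rule existed, and a check may exist in a document not shown. But the article is not silent here: it lists the exclusions, says twice that later aims use the same list, and states without qualification that Aim 2 adolescents will wear the glasses. An unlisted medication exclusion would make those statements wrong. None of the contact points is described as a medication screen, and contact with other providers depends on preferences found in Aim 1.

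It is also fair to say that Aim 3 use is inferred, that the number of affected adolescents is unknown, and that the article does not describe the harm. These points limit how large the problem can be shown to be. They do not remove the contradiction in Aim 2.

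**Conclusion.** The concern holds and should be corrected before Aim 2 enrols. For the 15 Aim 2 adolescents it rests on explicit text alone. For Aim 3 it is conditional: up to 50 further adolescents, if the finalised TSC keeps the light component. No estimate of the number actually on contraindicated drugs is possible from the article, and none is offered. The conclusion assumes only that the article's stated contraindication is correct and that the criteria are applied as written.

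**What to change.** Add the pilot's exclusion, current use of any photo-sensitizing medication, to the Aim 2 criteria now. Add it to Aim 3 if the finalised TSC retains the light component, and apply it before randomisation to both arms so that they remain comparable.

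Alternatively, leave the criteria identical across aims and state that the bright-light device is withheld from participants on these medications. Medication status would then be recorded before the device is issued in Aim 2 and before randomisation in Aim 3. This keeps those adolescents eligible for the rest of TSC.

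The cost is one criterion or one device rule, plus a medication check at enrolment. A few candidates would become ineligible or, under the second option, would receive TSC without the light component.

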#### Aim 2 measures

The primary Aim 2 outcomes pertain to intervention acceptability and feasibility. We will also pilot the sleep data collection methods and strategies to increase morning bright light and decrease evening light in anticipation of the Aim 3 randomized trial. Adolescents will wear actigraphs, Re-Timer glasses in the morning, blue-blocker glasses in the evening, complete a daily sleep diary, and provide ratings of their perceived sleep disturbances at pre and post intervention.

*Intervention acceptability* will be assessed at post-intervention using the adolescent self-reported Acceptability of Intervention Measure (AIM) (89). We will also conduct semi-structured qualitative interviews to identify participants' perspectives about intervention acceptability, barriers, and recommendations for additional adaptations to content or delivery strategies.

*Intervention feasibility* will be indexed by multiple outcomes (90), including the number of TSC sessions attended and rates of intervention attrition, to index intervention engagement. Intervention fidelity will be measured *via* the coding of a randomly selected 10% of video recorded TSC sessions. Sessions will be coded using the Cognitive Therapy Scale (CTS) (91) and a TSC session checklist (92), both used in prior TSC research.

*Actigraphy* is a widely used method of assessing sleep and circadian disruptions longitudinally in an individual's natural environment. Actigraphy is well-validated validated against polysomnography, the gold standard measure of overnight sleep (93). Consistent with guidelines, adolescents will continuously wear an actigraph on their non-dominant wrist, unless bathing or swimming, and complete a corresponding sleep diary for actigraphy scoring purposes. Sleep diary ratings will include time in and out of bed, sleep onset latency, night awakenings, and sleep quality (94). Actigraphy data will be scored using the Cole-Kripke algorithm in ActiLife software, which are validated against polysomnography and other actigraphs in young adults (95) and adolescents (96).

*Self-reported sleep disturbances* will be measured using the well-validated pediatric Patient-Reported Outcomes Measurement Information Systems (PROMIS) Sleep Disturbance and Sleep-Related Impairment Scales (97), which respectively measure perceived sleep difficulties and the impacts of sleep on daily functioning.

#### Aim 2 intervention procedures

TSC study clinicians will review the intervention manual and attend an initial 1-day training with the study investigators, who will conduct weekly supervision. The TSC developers ([name] and [name]) will consult on implementation as needed. Clinicians will interface with adolescents' other treatment providers and/or their caregivers in line with preferences identified in Aim 1. Therapist fidelity ratings (described above) will be monitored, with ratings < 80% prompting re-training with study investigators.

Study clinicians will implement core and optional modules weekly over 6–8 weeks *via* a HIPAA-compliant, secure telehealth platform. TSC sessions will supplement other mental health treatment that participants may be receiving. The selection and individualization of TSC models will be guided by the intake assessment, case conceptualization, adolescents' ongoing reports of sleep disturbances at sessions, and their actigraphy and daily diary data.

#### Aim 2 analytic approach

Our prior adaptation research (63, 66) and guidelines for thematic saturation (83) informed the Aim 2 sample size. As in Aim 1, we will monitor participant TSC ratings and qualitative feedback and increase our sample size if we do not reach thematic saturation. Aggregate mean AIM scores will be reviewed following each cohort of five participants. Scores for the final cohort will quantify overall acceptability, with high end-user acceptability identified as a mean AIM >80%.

